### Blinding

The patients and treatment providers will not be blinded. The blinding applies to researchers involved in assessments, data management, data analysis, and drawing outcome conclusions. For the follow-up interviews the patient is instructed in advance not to reveal what type of treatment was received.

### Statistical analyses

The planned comparisons between the two groups on continuous outcomes will be carried out with a generalised linear model adjusted for stratification variables, potential baseline imbalances, and skewed attrition, with missing data handled by multiple imputations. As an important secondary assessment of this type of outcome, linear mixed model analyses with repeated measurements and an unstructured covariance matrix will assess the interaction term between time and intervention. For non-normally distributed continuous outcome measures, non-parametric analyses will be applied. For dichotomous outcomes, logistic regression will be applied, and for time to transition, Cox proportional hazards regression will be applied. All analyses will be according to the intention-to-treat principle, analysing all participants in the groups they were assigned to by randomisation. We expect to encounter missing data, and this will be handled with the linear mixed models and multiple imputations as appropriate. A blinded and independent statistician who has no contact to the trial participants will conduct the primary efficacy analyses.

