### Assessments

Assessments will be conducted at baseline, prior to randomisation, as information from the baseline assessment is used to perform stratified randomisation and validate inclusion and exclusion criteria. The assessments will be performed at cessation of treatment 6 months after randomisation and at follow-up 12 months after randomisation.

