#### Neurocognitive function

Neurocognitive function will be assessed using a comprehensive test battery including the Danish Adult Reading Test (DART), a Danish adaptation of the National Adult Reading Test [51]; four subtests from the Wechsler Adult Intelligence Scale-Third Edition (WAIS-III) [51]; Vocabulary, Similarities, Block Design and Matrix Reasoning; the Brief Assessment of Cognition in Schizophrenia (BACS) battery [52]; and the Behavior Rating Inventory of Executive Functions-Adult Version (BRIEF-A) [53]. Furthermore, patients will undergo the following computerised tests from the Cambridge Neuropsychological Test Automated Battery (CANTAB) [51]: Motor Screening Test, Spatial Span, Spatial Working Memory, Emotion Recognition Task, Stockings of Cambridge, IED Set Shifting Test, Paired Associate Learning, 5-Choice Serial Reaction Time, and Rapid Visual Information Processing.

The BACS is specifically designed to detect cognitive changes in response to treatment. The validity and reliability properties of the BACS have been established in patients with schizophrenia and healthy controls, and the BACS composite score has proven high test-retest reliability, increasing the likelihood of detecting a treatment-related effect [52,54,55].

The tests included in the CANTAB battery have proven high validity [56,57]. The reliability of the CANTAB tests varies between individual tests. High reliability (*r* > 0.8) has been shown on measures of visual processing, e.g., the Paired Associates Learning task, while lower reliability has been found particularly on measures of executive functions, e.g., sub-measures of the IED Set Shifting Task [58]. This lower reliability of tests that assess executive functions is very difficult to avoid because of the necessary task novelty involved in assessing executive processing [58].

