### Outcomes and sample size calculation

#### Primary outcome

The primary outcome is overall cognitive function, measured with the BACS composite score 6 months after randomisation.

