### Sample size calculation

The sample size calculation is based on our primary outcome, a priori defined to be the between-group difference at 6 months on the BACS composite score. We consider a clinically relevant difference on this scale to correspond to a Cohen’s *d* of 0.50 (e.g., assuming a between-group difference of 3.0 and a pooled SD of 6.0) [29]. With a two-sided alpha of 0.05 and power of 80%, this will require 63 participants to be randomised to each of the two interventions.

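### Primary-model covariates beyond the stratifiers are chosen by observed imbalance and attrition, so baseline BACS is not a fixed covariate and the model is not known until the data are seen

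*Protocol article*

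**What the plan says.** The Primary outcome section states: "The primary outcome is overall cognitive function, measured with the BACS composite score 6 months after randomisation". The Sample size calculation treats this as a plain two-group comparison, "assuming a between-group difference of 3.0 and a pooled SD of 6.0", with no reduction of the SD for baseline information.

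For continuous outcomes, the Statistical analyses section sets a "generalised linear model adjusted for stratification variables, potential baseline imbalances, and skewed attrition, with missing data handled by multiple imputations". The Randomisation section gives the stratifiers as current antipsychotic use (yes/no) and IQ (at most 100, or above 100). Baseline BACS is neither a stratifier nor a named covariate.

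The score will nevertheless be available. The Assessments section says: "Assessments will be conducted at baseline, prior to randomisation". The BACS is part of the neurocognitive battery, and the section on that battery says that "the BACS composite score has proven high test-retest reliability, increasing the likelihood of detecting a treatment-related effect".

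A repeated-measures mixed model is planned as an important secondary assessment, and a blinded, independent statistician will run the primary efficacy analyses.

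**The concern.** In a randomised trial, a baseline covariate earns its place by predicting the outcome. Whether it happens to differ between arms is a poor criterion: a strong predictor that is well balanced still removes residual variance, and a weak predictor that is imbalanced contributes almost nothing. The sentence in the plan uses the poor criterion.

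Two things follow. First, the most obvious predictor of the 6-month BACS composite is its own baseline value, and the model as written includes it only if it is judged imbalanced. The protocol relies on the reliability of the BACS to help detect an effect, but a comparison of 6-month scores draws on the stability of a person's score only when baseline is in the model. Second, which variables are imbalanced, and which relate to uneven dropout, is unknown until baseline and follow-up data are complete. Several different primary estimates are therefore compatible with the same text. At stake are the precision and the pre-specification of the primary result.

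**Working it through.** **Inputs from the protocol.** Difference 3.0, SD 6.0, so d = 0.50; two-sided alpha 0.05; 63 per arm. **Assumed, because the document gives no figure:** the correlation ρ between baseline and 6-month BACS, taken as 0.5 to 0.8; the correlation q between IQ and BACS, taken as 0.3 to 0.6.

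**Step 1: the plan's own figure.** n per arm = 2(1.960 + 0.842)² / 0.50² = 62.8, so 63. This reproduces. The exact t-test gives 79.5% power at 63 per arm and 80.1% at 64.

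**Step 2: baseline BACS as a fixed covariate.** The residual SD is 6.0 × √(1 − ρ²), so the effective d is 0.50 / √(1 − ρ²). Noncentral-t power with 63 per arm:

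| ρ | Variance removed | Residual SD | Effective d | Power |
|---|---|---|---|---|
| none | 0% | 6.00 | 0.500 | 79.5% |
| 0.5 | 25% | 5.20 | 0.577 | 89.5% |
| 0.6 | 36% | 4.80 | 0.625 | 93.6% |
| 0.7 | 49% | 4.28 | 0.700 | 97.4% |
| 0.8 | 64% | 3.60 | 0.833 | 99.6% |

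**Step 3: what the planned stratifiers already recover.** The plan is not unadjusted, because IQ is in the model. If IQ is split at its median, the split variable has correlation b = q√(2/π) with BACS, and R² = b². For q = 0.3, 0.5 and 0.6, R² is 0.057, 0.159 and 0.229, and power with the strata alone is about 82%, 86% and 89%. Antipsychotic use is taken to add nothing. With both the IQ split and baseline BACS, R² = (ρ² + b² − 2ρb²) / (1 − b²). At ρ = 0.5 this is 0.265 to 0.324, for power of 90% to 92%. At ρ = 0.7 it is 0.495 to 0.517, for power of about 98%.

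The fair comparison is therefore 82% to 89% against 90% to 92% at ρ = 0.5, and 82% to 89% against about 98% at ρ = 0.7.

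**Step 4: selection by imbalance.** Simulation with 63 per arm and normal data, without strata (100,000 null and 60,000 alternative replicates for each ρ). Baseline enters only if its between-arm p-value is below 0.05, or below 0.20. The last column takes the smaller of the unadjusted and adjusted p-values.

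| ρ | Power, always adjust | Power, rule 0.05 / 0.20 | Size, rule 0.05 / 0.20 | Size, free choice |
|---|---|---|---|---|
| 0.5 | 89.2% | 80.5% / 82.6% | 4.3% / 3.7% | 7.3% |
| 0.6 | 93.4% | 81.0% / 84.2% | 4.1% / 3.3% | 7.8% |
| 0.7 | 97.3% | 81.6% / 86.0% | 3.6% / 2.6% | 8.2% |
| 0.8 | 99.6% | 81.7% / 87.3% | 3.1% / 2.0% | 8.7% |

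A mechanical imbalance rule is conservative and recovers little of the available power. Discretionary choice is anti-conservative. Always adjusting held its size at 5.0% to 5.1%.

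**The case against.** The strongest reply is that this is a condensed article, that covariate lists commonly sit in an analysis plan that is not shown, and that nothing here forbids baseline BACS. That is fair as far as it goes, and an unseen plan may already name it. But the point rests on what the sentence states, namely a selection rule based on imbalance and attrition. An analysis plan that followed it faithfully would inherit the problem.

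The size can also be challenged, and much of that challenge stands. The planned model already contains an IQ split, so comparison with an unadjusted test overstates the gap (step 3). High test-retest reliability, which the protocol says was established in schizophrenia and healthy controls, is not a 6-month correlation in ultra-high-risk patients. The trial also reaches its stated 80% power, within rounding, with no covariate at all, so this is forgone efficiency and not a shortfall.

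Inflation of type I error needs someone to choose freely between results. The independent statistician is blinded, which makes motivated choice less likely. Blinding does not, however, say which model is to be fitted.

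Some stronger readings are tempting but unsupported:

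- **Most of the precision is lost.** This would need ρ² above 0.5, that is ρ above about 0.71, and no ρ is given.
- **Nothing else informs the conclusion.** The mixed model is planned for the same outcomes and uses repeated measurements.
- **Adjusting for attrition must bias the estimate.** The phrase may simply mean baseline variables related to dropout. No post-randomisation covariate is named.
- **The mixed model is an underpowered joint test over all visits.** The text says only that it "will assess the interaction term between time and intervention". It fixes neither the visits nor the degrees of freedom, and the power of such a test depends on the correlation and on how long the effect lasts.

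**Conclusion.** The concern holds in this form: the primary model's covariates beyond the stratifiers are chosen by observed imbalance and attrition, baseline BACS is not fixed among them, and the primary model cannot be written down before the data are seen.

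The precision at stake depends on two assumed correlations. Over the ranges used, the realistic gain from fixing baseline BACS runs from a few percentage points of power (89% to 92% at ρ = 0.5 with a strongly related IQ split) to about 16 points (82% to 98% at ρ = 0.7 with a weakly related one). The effect on the error rate can go either way: size of about 2% to 4% under a mechanical rule, or about 7% to 9% under free choice between two p-values. Neither delivers the nominal 5%. This does not show that the trial is underpowered by its own figures or that its estimate will be biased.

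**What to change.** State the primary model as the 6-month BACS composite regressed on treatment, the continuous baseline BACS composite, antipsychotic use and the IQ stratum. Analyse each secondary scale in the same way, with its own baseline value. Move any adjustment for observed baseline imbalance to labelled sensitivity analyses. Put baseline predictors of dropout in the multiple-imputation model, not among the covariates of the outcome model.

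The cost is about one sentence in the analysis plan, agreed before unblinding. It needs no further patients and no further data, because the baseline assessment is already scheduled. If an existing analysis plan already fixes this model, it is enough to say so and to bring the protocol wording into line.

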**Methods:**

The FOCUS trial (Function and Overall Cognition in Ultra-high risk States) is a randomised, parallel group, observer-blinded clinical trial enrolling 126 patients meeting the standardised criteria of being at UHR for psychosis. Patients are recruited from psychiatric in- and outpatient facilities in the Copenhagen catchment area. Patients are randomised to one of the two treatment arms: cognitive remediation plus standard treatment versus standard treatment. The cognitive remediation consists of 24 weekly group-based and manualised sessions targeting neurocognition and social cognition. In addition to the group sessions, the patients will be offered 12 individual sessions aiming at maximising the transfer of the effects of the cognitive training to their everyday lives. Follow-up assessments will be conducted at 6 and 12 months after randomisation. The primary outcome is the composite score on the Brief Assessment of Cognition in Schizophrenia at cessation of treatment after 6 months. Secondary outcomes are social and daily functioning, psychosis-like symptoms, negative symptomatology, and depressive symptomatology as measured with the Personal and Social Performance Scale, Brief Psychiatric Rating Scale-Expanded Version, Scale for the Assessment of Negative Symptoms, and the Montgomery-Åsberg Depression Rating Scale.

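### The secondary mixed model's time-by-intervention interaction, on its conventional reading, is a change-from-baseline contrast and gives up precision that a common baseline mean would recover at no cost (free improvement, minor)

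*Protocol article*

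**What the plan says.** The section Statistical analyses of the protocol article plans two analyses for continuous outcomes. The main comparison is a "generalised linear model adjusted for stratification variables, potential baseline imbalances, and skewed attrition, with missing data handled by multiple imputations". The second is introduced with "As an important secondary assessment of this type of outcome", and in it "linear mixed model analyses with repeated measurements and an unstructured covariance matrix will assess the interaction term between time and intervention".

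The timing of the measurements is fixed elsewhere. Under Assessments, "Assessments will be conducted at baseline, prior to randomisation"; in the Methods paragraph of the abstract, "Follow-up assessments will be conducted at 6 and 12 months after randomisation". The section Sample size calculation defines the primary effect differently from an interaction: it is "a priori defined to be the between-group difference at 6 months on the BACS composite score", that is, a contrast of month-6 scores.

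The article does not say whether baseline is one of the repeated responses, whether the arms may differ at baseline in the model, or whether the interaction is read at month 6, at month 12 or jointly. It gives no correlation between baseline and follow-up for any scale. The nearest statement, under Neurocognitive function, is that the "BACS composite score has proven high test-retest reliability".

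**The concern.** The tested term is named, and it answers the efficacy question only if baseline is among the responses. If the responses were months 6 and 12 alone, the interaction would ask whether the effect changes after treatment ends, which is not the month-6 question on which the trial is sized.

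With baseline as a response, the conventional model has time, intervention and their interaction, so each arm has its own baseline mean. The month-6 interaction then subtracts the observed baseline difference in full. Because baseline is measured before randomisation, the true difference is zero. Subtracting an estimate of a known zero with weight 1, where the best weight is r, adds noise.

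At stake is the precision of an analysis that the article itself calls important, on every continuous outcome: the BACS composite and the PSP, BPRS-E, SANS and MADRS. It is also one of the two means by which the article intends to handle missing data.

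**Working it through.** **Inputs from the article.** 63 per arm, two-sided alpha 0.05 and d = 0.50, from "assuming a between-group difference of 3.0 and a pooled SD of 6.0" (Sample size calculation). Under Secondary outcomes and power calculations: PSP, SD 10 and a difference of 7; BPRS-E, SD 20; SANS, SD 13; MADRS, SD 10.

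**Assumptions.** Equal SD at all visits and complete data. r is not in the article, so a range is shown.

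**Step 1: the article's own figures.** They reproduce as month-6 two-sample comparisons.
- For d = 0.50 the normal formula gives 63 per arm. Power at 63 is 80.1% (normal) or 79.5% (t).
- PSP power is 97.4% (t), against the stated value of more than 97%.
- Detectable differences at 80% power (t) are 10.06 (BPRS-E), 6.54 (SANS) and 5.03 (MADRS), as stated.

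**Step 2: variance of the month-6 effect**, in units of σ²(2/n), so that a month-6 comparison ignoring baseline has value 1.
- Interaction with free baseline means: Var(Y6 − Y0) = 2(1 − r)
- Common baseline mean, or baseline as covariate: 1 − r²
- Ratio: 2(1 − r)/(1 − r²) = 2/(1 + r)

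Generalised least squares on three visits with a compound-symmetric covariance gave the same values: 1.40 v 0.91 at r = 0.3, 1.00 v 0.75 at r = 0.5, and 0.40 v 0.36 at r = 0.8.

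**Step 3: size over a range of r.** Power is for d = 0.50 and 63 per arm: Φ(0.50·√(63/2)/√v − 1.96), with v the relative variance. Ignoring baseline, it is 80.1% throughout.

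| r (assumed) | v, free baseline | v, common baseline | excess variance | power, free | power, common |
|---|---|---|---|---|---|
| 0.3 | 1.40 | 0.91 | 54% | 66.0% | 83.7% |
| 0.4 | 1.20 | 0.84 | 43% | 72.6% | 86.5% |
| 0.5 | 1.00 | 0.75 | 33% | 80.1% | 90.0% |
| 0.6 | 0.80 | 0.64 | 25% | 88.1% | 93.9% |
| 0.7 | 0.60 | 0.51 | 18% | 95.2% | 97.6% |
| 0.8 | 0.40 | 0.36 | 11% | 99.3% | 99.7% |
| 0.9 | 0.20 | 0.19 | 5% | about 100% | about 100% |

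The free-baseline contrast falls below a plain month-6 comparison when 2(1 − r) > 1, that is, when r < 0.5.

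**Step 4: the secondary scales on their own figures.** d = 0.50 is the BACS assumption and should not be carried over to the other scales. At an assumed r = 0.4, power by the t distribution is:
- PSP, 7/10 = 0.70: 94.5% free, 98.9% common.
- BPRS-E, using the 12-point reduction that the article cites, 12/20 = 0.60: 86.2% free, 95.4% common.
- SANS, using the 7-point reduction that the article cites, 7/13 = 0.54: about 78% free, about 90% common.

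For SANS in points, the detectable difference at r = 0.4 is 6.54 × √1.20 = 7.2 with free baseline means and 6.54 × √0.84 = 6.0 with a common mean. The article's benchmark is a reduction of more than 7 points.

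**The case against.** The strongest reply is that the free baseline means are inferred. The sentence names a term, not a parameterisation, and a model with a common baseline mean also has intervention-by-visit effects that could be described in the same words. How baseline enters is often settled in a statistical analysis plan, which is not shown here. This stands in part: the plan may already do what is proposed. The point therefore rests on the conventional reading of a term that the article chose to name, and not on missing detail.

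Second, a change-from-baseline contrast is unbiased under randomisation and its test is valid. The mixed model is secondary, and the planned sample size does not depend on it. This stands in full.

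Three stronger readings are tempting, and the article does not support them.
- *The analysis is generally weaker than ignoring baseline.* That needs r below 0.5. No r is given for any scale, and the reliability statement for the BACS composite points the other way.
- *After a chance baseline imbalance, the main and secondary analyses move in opposite directions.* That holds only against an end-score comparison not adjusted for baseline. The main model is to adjust for potential baseline imbalances. If that covers the baseline outcome, its estimate is already corrected.
- *A common-baseline model keeps participants who have only a baseline value, and so gains on the current one.* The conventional mixed model with baseline as a response keeps them too.

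**Conclusion.** The point holds as a free improvement of minor severity. Read conventionally, the secondary mixed model tests a contrast with 2/(1 + r) times the necessary variance. The excess runs from 54% at r = 0.3 to 5% at r = 0.9, and all values of r are assumptions. For the BACS composite, if r lies between 0.7 and 0.9, the excess is 5 to 18% and power for d = 0.50 is above 95% either way. The benefit would fall mainly on functioning and symptom scales with lower r, and even there it depends on the scale: PSP keeps over 94% power at r = 0.4, while for SANS the detectable difference moves from one side of the cited 7-point benchmark to the other.

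The figures assume equal variances and complete data. With missing data the interaction is no longer exactly the difference in mean change, so the ratios are a guide. What is lost is precision in a secondary analysis. There is no bias, the sample size of 63 per arm stands, and the primary analysis is untouched.

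**What to change.** In Statistical analyses, or in the statistical analysis plan, add one sentence to this effect: the mixed model keeps its unstructured covariance and has baseline, month 6 and month 12 as responses; the arms share a common baseline mean, with intervention effects at months 6 and 12 only; the month-6 intervention effect is the tested contrast, and the month-12 effect is reported as follow-up.

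An acceptable alternative is to take months 6 and 12 as the responses and enter the baseline outcome as a covariate by visit. In that form the tested effect must be stated as the month-6 intervention contrast and not as the interaction, because the interaction would then compare month 12 with month 6.

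The cost is one sentence. No new data are needed, and the constraint relies only on baseline preceding randomisation. Trial status reports 19 patients randomised by November 2014 out of the 126 planned, so at that point the wording could be settled well before any unblinded analysis. If the statistical analysis plan already specifies one of these forms, nothing needs to change.

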### Ethical consideration

The trial has obtained approval by the Regional Ethics Committee of Zealand (H-6-2013-015) and the Danish Data Protection Agency (RHP-2014-009-02670). The trial is registered at ClinicalTrial.gov as NCT 02098408. Positive as well as neutral and negative results of the trial will be published in international journals.

The participants will receive information on the trial both verbally and in written form. Written informed consent will be obtained from each participant before inclusion in the trial. It is emphasised that participation in the trial is voluntary and that the participant can withdraw his or her consent at any time without consequences for treatment possibilities. We will upload depersonalised individual patient data to be used in meta-analyses on Zenodo via OpenAIRE (https://www.openaire.eu/).

